### Measures

2.3

Relevant biographical data are collected at baseline within a clinical interview. They included the children’s age at the first out-of-home placement, substance use dependency syndrome of biological parents and the number of caregivers since out-of-home placement. Data Research Topic is conducted by specifically trained clinical psychologists and psychotherapists.

#### Primary outcome

2.3.1

Caregiver and child Reflective Functioning (RF) are assessed by a licensed coder using the Reflective Functioning Scale (RFS) (Fonagy et al., 1998; Shmueli-Goetz et al., 2011) to interpret predefined sections of the Adult Attachment Interview (AAI) (George et al., 1985), and using the Child Reflective Functioning Scale (CRFS) (Target et al., 2001) to interpret the Child Attachment Interview (CAI) (Shmueli-Goetz et al., 2008) transcripts. The AAI and the CAI, semi- structured clinical interviews focus on the subject’s attachment experiences with their parents during childhood. Some questions in the AAI (e.g., “Why did your parents behave as they did during your childhood?,” “Do you think your childhood experiences have an influence on who you are today?”) and some questions in the CAI (e.g., “Do your parents sometimes argue? How do they feel? Why do you think they do that?” or “What happens when your mum gets cross with you or tells you off? How do you feel?”) require reflective functioning (RF), while others allow it. According to Fonagy et al. (1998), RF occurs when the interviewee shows (1) awareness of the nature of mental states, (2) an explicit effort to tease out the mental states underlying one’s own and others’ behavior and (3) the tendency to recognize developmental aspects of mental states over time or (4) mental states in relation to the interviewer. After rating each identified passage of the AAI, an overall score is assigned to each interview ranging from −1 (negative RF) to 9 (exceptional RF) (Taubner et al., 2013). The same procedure will be conducted for the CAI.

After rating each identified passage of the CAI, an overall classification is assigned to the interview, using a hierarchical approach, and distinguishing between 10 levels of RF, ranging from −1 (negative RF) to 9 (exceptional RF) (Ensink et al., 2013).

Validation studies of the RFS (Fonagy et al., 1998; Ensink et al., 2015) proved discriminant and predictive validity and good interrater reliability. Temporal stability of children’s RF was shown to be high over a 3-month period and adequate over 12 months (Ensink, 2004).

#### Secondary outcomes

2.3.2

To investigate the children’s mental health, their clear-thinking ability, and their dynamic personality structure, as well as the caregiver’s attitudes on drugs and drug addiction and their social skills (e.g., social orientation and reflexibility) the following measures are chosen:

The Child Behavior Checklist (CBCL/6-18R) is a parent report form to screen for emotional, behavioral, and social problems in children, based on the DSM-IV (Esser and Hänsch-Oelgart, 2018). A DSM-5 oriented version is not yet available. For the aim of the present study the presence of the following psychiatric disorders from the Diagnostic and Statistical Manual of Mental Disorders IV (American Psychiatric Association, 1994) were assessed: anxiety, oppositional defiant disorder, conduct problems, somatic problems, affective problems, and attention deficit disorder. The profiles show raw scale scores derived by the sum of each item. The scales are quantitatively scored in terms of gender- and age-specific t-scores with cut points for normal (t-scores from 50 to 64), borderline (t-scores from 65 to 69), and clinical (t-scores from 70 to 100) ranges (Döpfner et al., 2014). The CBCL is widely used in clinical research and diagnostical practice and shows good results regarding reliability and validity (Nakamura et al., 2009).Raven’s Colored Progressive Matrices (RCPM) measures clear-thinking ability and is designed for young children aged 5–10 years and older adolescents. The RCPM is internationally recognized as a culture-fair test of nonverbal (fluid) intelligence. The test consists of 36 items clustered in 3 sets (A, Ab, B), with 12 items per set. Most items are presented on a colored background to make the test visually stimulating for participants. The RCPM produces a single raw score that can be converted to a percentile based on normative data, designating the following categories: Performance Level 1 “well above average” (>95 percentile); Performance Level 2 “above average”(percentiles 75–95); Performance Level 3 “average” (percentiles 25–75); Performance Level 4 “well below average” (percentiles 5–25); Performance Level 5 “intellectual disability” (percentiles <5) (Bulheller and Häcker, 2002). In daily clinical practice, RCPM test is used as one of the best general intelligence measures (Smirni, 2020).The social orientation and Reflexibility subscales of the 33 items- Inventory of Social Competences (ISK; Inventar sozialer Kompetenzen) by Kanning (2009) is used to assess the caregiver’s social skills. The raw-data analysis is standardized by means of an evaluation form. The 17 raw scores of the primary scales and the four total raw scores of the secondary scales are transformed into stanine scores with the help of standard tables (Kanning, 2009). The reliability of the instrument can be rated as satisfactory to good. Numerous results from several individual studies on convergent and discriminant validity are reported (Scherp, 2010). For this study, we focus on the two subscales social orientation and reflexibility.The Patte-Noire (“black paw”) -Test is a French thematic-projective test for children from 6 to 12 years: a storytelling test through the character of the little pig Patte Noire, used in children’s clinical assessment, to elicit themes related to the child’s perceptions of the relationships between parents and children, and siblings and to obtain unconscious material. The test is administered according to Corman (1972) criteria in two main parts: telling a story and identifications. The child is asked to look at 17 different panels that show pigs in social situations, to choose one or more of them, to tell a story about “Patte Noire” and also to tell with which character on the panels he/she identifies—if possible. While working on the story, the child has to put him/herself in the situation described by the panels. In each panel one little pig is marked with a black paw. Every panel stimulates one of the following themes: orality, anality, oedipal issues, aggression, dependency-independence, guilt, black spot, inverted sexes, nurturing father, ideal mother. For the purposes of this study, 7 sheets out of the total 17 comprising Corman’s Patte Noire Test have been selected to take a look at the identifications in terms of attachment relations as it was already conducted and published by Ballus et al. (2019). The 7 selected pictures express clearly attachment relations in terms of attachment theory (Corman, 1977; Ainsworth et al., 1978; Bowlby, 1982; Yarnoz, 1993) and were selected in order to elicit information about the children’s attachment experiences, for example panel N°4: “the Cart.” Patte Noire (PN) dreams that a farmer is taking some piglets away in a cart. PN’s parents and two other piglets watch the scene. Theme of separation and loss. The childrens’ identifications on panel N°4 (“the cart”) in relation to the foster care situation has our special interest looking at the children’s identifications with the little pig (“Patte Noire”) or with “No One” or with somebody outside the scenery on the panel. This test is highly recommended by child psychoanalysts and is frequently used for clinical psychological diagnosis in addition to clinical psychological tests.Attitudes to Drug Use (ADU) (Harmon, 1993). A German version, translated and retranslated by expert native speakers, of a non-standardized 12-items paper-pencil-questionnaire is used to assess the caregiver’s attitudes to drug use on a 5-point-rating scale ranging from 1 (strongly disagree) to 5 (strongly agree). The questions are formulated as statements such as “using illegal drugs can be pleasant” or “trying drugs is losing control of your life.” Computation of Indices: Items (a), (d), (e), (i), (k), were scored “5” for “strongly agree” to “1” for “strongly disagree,” while the other items (−) were scored in the opposite way (1 for “strongly agree” to “5” for “strongly disagree”). To obtain an attitude score for each individual, the scores for each item were summed and divided by the number of items answered. A score of 5.00 indicates a completely positive attitude toward drugs while a score of 1.00 indicates a completely negative attitude. In accordance with Hulin et al. (2001), the internal reliability of this scale is within a very good range (α = 0.89).

### Procedure

2.4

The study is conducted by the Faculty of Psychology of the University of Vienna in collaboration with the NGO Dialog.^1^ The study was approved by the Ethical Committee of the University of Vienna (#00295). All procedures performed in the study follow the ethical standards of the institutional and/or national research committee and are in agreement with the Helsinki Declaration and its later amendments or comparable ethical standards. Written informed consent is obtained from the foster parents or legal guardians, and assent from children is gained as well.

Officially registered with the DRKS (German Clinical Trials Register) #DRKS00027868, the trial is displayed on the public website. It has been submitted to the WHO and is searchable through its meta-register.^2^ Caregiver and child Reflective Functioning (RF) are assessed by a licensed coder using the Reflective Functioning Scale (RFS) (Fonagy et al., 1998; Shmueli-Goetz et al., 2011) to interpret predefined sections of the Adult Attachment Interview (AAI) (George et al., 1985), and using the Child Reflective Functioning Scale (CRFS) (Target et al., 2001) to interpret the Child Attachment Interview (CAI) (Shmueli-Goetz et al., 2008) transcripts.

The trial site is the outpatient center of the NGO Dialog in Vienna (A), where the mentalization-based group intervention was developed and takes place. This NGO specializes in prevention and treatment of substance use disorders for more than 40 years.

Participants follow a 20-week mentalization-based group intervention aiming at increasing knowledge about drug addiction and at enhancing social and affective skills in children (6–12 years) of drug abusing families living in foster care. The participation in the study is voluntary. Data are collected at baseline (T1), within 1 month after treatment termination (T2) and at 12 months follow-up (T3) (Figure 1).

**Figure 1 fig1:**
[figure not shown]
Study flow chart. Sequence of steps from T1 to T3.

### Mentalization-based group intervention

2.5

Findings from a cross-European study conducted in 2007 on Domestic Violence and Abuse among Adolescents from Alcohol-affected Families indicated that adolescents expressed the value of being in relation with others who have undergone similar experiences or have faced similar challenges within their families. They perceived these interactions beneficial specifically in realizing that they were not alone in these circumstances (Velleman et al., 2008). The mentalization-centered group model offers a secure and contained environment, akin to a *relational laboratory*, in which children can safely investigate their thoughts and emotions regarding their real-life situations and emotional challenges (Malberg, 2012).

The Mentalized-Based Group Intervention (MBGI) was adapted from the MBT-C by Midgley et al. (2017) to the particular needs of children of drug abusing parents living in foster care in middle childhood. In accordance with other short-term interventions, such as “SMART” (Fearon et al., 2006) or “Trampolin” (Wiedow et al., 2011), ten group sessions for children and three group sessions for the foster caregivers are provided by specifically trained psychotherapists in a period of 5 months (school semester). The facilitators have attended trainings at the Anna Freud Centre in London (UK) on *“Mentalizing and Mentalization Based Treatments with Children, Young People and Families (MBT CYP)”* as well as *“Reflective Parenting (MBT-RP).”* Each session lasts about 90 min. The first encounter with the caregivers takes place after the first children’s group session to get to know each other, to obtain a first impression of the group by the psychotherapists, and to introduce mentalization processes to the caregivers in order to make them part of the children’s support. The second caregiver session is, scheduled halfway through the intervention. It is used to reflect on the ongoing treatment and its impact on the children’s daily lives. The final group session with the caregivers serves as a review of the experience and a preview of future intervention opportunities. The three caregiver sessions include information on parental licit/illicit drug abuse background focusing on the caregiver-child-interaction, along the process described by Fonagy and Allison (2014): (1) development of a therapeutic context in which the children/caregivers feel understood to reduce the sense of epistemic trust; (2) reemergence of the participants’ capacity to mentalize, as they “find their mind in the mind of the therapist”; (3) being aware of and interested in the content of the psychoeducational work of the therapists and to benefit from the group as a place to share experiences.

For the children, the 10 group sessions follow a ritualized procedure: there are predefined contents, such as drug addiction in general, the children’s situation in foster care, their feelings toward their biological parents and their foster caregivers. Since group dynamics in the sessions are never predictable, there is always time for “open topics,” brought up by the children. Group sessions are always conducted in the same room, which does not contain too many distracting elements but is large enough to allow for physical games like throwing and catching a ball or play “Emotion-Charade,” where children try to nonverbally pantomime a pre-selected emotion to each other. The material provided to the children involved painting, drawing and sketching tools. Children are invited to talk or to express themselves and their feelings by using available materials. Drawing is particularly useful, feels to be less intrusive and threatening than the request to talk about one’s experiences (Gardner and Harper, 1997).

The aims of the group sessions are (1) restoring the frame to think and talk about highly affective feelings such as anger, fear and shame, (2) building up a small and safe mentalizing community to explore mental states and giving sense to the behavior of oneself and others, (3) discussing the individual meaning and consequences of the experience of parental substance use or parents being “high” on licit/illicit drugs, and (4) providing new ego-strengthening skills.

The ritualized procedure contains a welcome circle that allows space for current events or feelings, planned psychoeducational inputs, and a special feedback method to recap what was discussed in each session and gather the children’s opinions on it.

The psychoeducational input always contains an interactive play or method.

As outcome of this Mentalization-Based Group Intervention, we expect a decrease in children’s psychiatric symptoms as there is evidence from previous studies on the effects of Mentalization-Based Interventions (Åkerman et al., 2020; Dalgaard et al., 2023). Furthermore, we expect an increase in the RF Score (capacity to mentalize). It has been shown that the RF Score can change as a result of psychotherapy, especially in psychodynamic oriented psychotherapy. These results have been observed, using the AAI to gain the RF Score (Katznelson, 2014).

### Statistical plan and data analysis

2.6

Sociodemographic data will be used to characterize the sample and to provide an in-depth look into the participant’s psycho-social background. Frequencies and means are derived for demographic variables.

Thresholds for the measures will be used to describe each case, and to provide descriptive statistics, such as frequencies, mean and standard variation (SPSS 27.0), for each group: caregivers, children living in foster families and children living in institutional foster care.

Analyses on quantitative data will be conducted using the statistical software SPSS (IBM, Version 27.0).

All statistical analyses will consider the type of data available. Therefore, the primary outcome of the study will be assessed via the Friedman test as it is the non-parametric alternative to the one-way ANOVA with repeated measures, to compare the changes in reflective functioning scores between the pre-intervention, post-intervention, and one-year follow-up assessments, with the group (family foster care vs. residential programs) as a between-subjects factor and the time of assessment (pre, post, follow-up) as a within-subjects factor. In addition, the Mann–Whitney U test is used to compare differences between two independent groups (foster family and institutional foster care). To assess potential correlations regarding the child and caregivers’ capacity to mentalize, Spearman correlations (ρ) are conducted.

For the secondary outcome variables we choose a mixed-method approach for data analysis. Qualitative data from the “Patte-noir” will be processed via qualitative thematic analysis (Braun and Clarke, 2006). To provide an in-depth understanding of the psycho-social background of foster children and their foster caregiver, taking into account the caregivers’ social competences, their attitudes to drugs and drug addiction and the children’s mental state, quantitative methods, equal to the ones for the primary outcome variables, will be used.

This mixed-method approach was chosen to obtain different and multiple perspectives to validate the results and to build a comprehensive understanding.

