**Discussion:**

The present study uses the current research concept of mentalization to identify affective and cognitive abilities of the caregiver-child dyad with the aim of compensating deficits on both sides with psychological-psychotherapeutic strategies. There are some limitations of the study to mention: the small sample size does not allow to generalize the results. Due to the lack of a comparison group, a randomized control study (RCT) was not conducted. The authors are aware of these limitations. However, the studies’ findings, will help to deduce research questions for further studies.

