Specifically, those children who experienced trauma frequently revealed underdeveloped mentalizing capacities (Ostler et al., 2010). Muller et al. (2012) specified that their ability to cope with physical, or emotional traumas highly correlated with the perceived quality of their current relationships, and that traumatic experiences had a major impact on attachment behaviors of out-of-home children toward their foster caregivers. As a result of the children’s adverse experiences with parental care, they may be inclined to avoid forming new and supportive relationships. This creates a complex situation for all individuals involved, including both the foster caregiver and the children. On the other side, foster parents and institutional caregivers know that foster care is mostly not permanent. This issue may interfere with attachment formation to the foster parents/caregivers (Åkerman et al., 2020).

The ability to mentalize plays a crucial role in individuals’ coping abilities with traumatic events (Pecora et al., 2005; Szilagyi et al., 2015). Mentalization can be understood as “the ability to understand the actions by both other people and oneself in terms of thoughts, feelings, wishes and desires” (Bateman and Fonagy, 2016, p. 3). By involving the internal regulation of emotions through thoughts, children as well as adults who are able to mentalize are more resilient and able to tolerate feelings of anger, fear, shame, and distress resulting from adversity and trauma (Allen et al., 2008; Brockmann and Kirsch, 2010; Ostler et al., 2010; Ensink et al., 2017; Giusti et al., 2021).

Research revealed a strong association between insecure attachment representations and struggles of drug addicted parents in responding to their children’s emotional cues (Grienenberger et al., 2005; Slade et al., 2005), which in turn interfere with the ability to form secure attachments and mentalizing skills in children (Madigan et al., 2007; Bammens et al., 2015). However, most studies have focused mainly on the characteristics of the child, neglecting the parents’ variables (Schmidt and Schimmelmann, 2015).

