### Participants

2.2

In the study 30 children living in foster care (institutional or foster home) and their actual main foster caregiver will be included (*N* = 60).

Children’s inclusion criteria for participation are: (1) age between 6 and 12 years, (2) stable mental health status (e.g., no psychotic state), (3) living in foster care for at least 6 months. A minimum of time in a stable and persistent placement needs to be considered to assure the children’s ability to reorganize their internal world and behavioral outcomes (Cassibba et al., 2023). Caregiver’s inclusion criteria are (1) child lives in the same household and (2) 18 years of age or older. Children are excluded from the study if presenting neurological, cognitive, and/or psychiatric problems, and/or difficulties reported by their caregiver.

Children in middle childhood, aged between 6 and 12, are very common as primary target of mentalization-based treatments. However, middle childhood has received only limited attention regarding the ability to mentalize (Midgley et al., 2021).

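### The primary Friedman test across T1, T2 and T3 discards the observed pre-post change of every child not seen at the 12-month follow-up; how many children and in which direction cannot be told from the protocol

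*Protocol article*

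**What the plan says.** Section 2.6 (Statistical plan and data analysis) fixes the primary test: "the primary outcome of the study will be assessed via the Friedman test as it is the non-parametric alternative to the one-way ANOVA". Its purpose is "to compare the changes in reflective functioning scores between the pre-intervention, post-intervention, and one-year follow-up assessments". The abstract names the same test and justifies it by the ordinal outcome.

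On timing, section 2.4 (Procedure) says: "Data are collected at baseline (T1), within 1 month after treatment termination (T2) and at 12 months follow-up (T3"). The same section makes participation voluntary. On numbers, section 2.2 (Participants) says: "In the study 30 children living in foster care (institutional or foster home) and their actual main foster caregiver will be included". The expected direction is in section 2.5: "Furthermore, we expect an increase in the RF Score (capacity to mentalize"). On design, the abstract says: "Due to the lack of a comparison group, a randomized control study (RCT) was not conducted".

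On the stability of placements, the Introduction remarks that "foster parents and institutional caregivers know that foster care is mostly not permanent".

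The article gives no expected dropout, no RF standard deviation, no effect size and no power. It describes no separate T1-T2 analysis on all available pairs.

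**The concern.** The Friedman statistic ranks the three visits within each child. With one visit missing there is no complete set of ranks, and the child leaves the analysis altogether. Suppose a child attends all ten sessions, gives interviews at T1 and T2, and has moved by T3. That child adds nothing to the primary result, although the immediate pre-post change was measured.

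Two things are at stake. The first is precision: the study has 30 children, so each lost row matters, and the pre-post question is tied to attendance a year later. The second is possible bias. There is no concurrent comparison group, so the conclusion rests mainly on within-child change. If attendance at T3 is related to benefit, the completers' change differs from the change in all children who were treated and re-interviewed. The historical control data mentioned in the Discussion would not repair a selection inside this cohort.

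**Working it through.** **The plan's own figure.** The only figure is 30 children. It comes without effect size, SD, alpha, power or dropout, so it cannot be reproduced.

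**Step 1: the test needs complete triples.** In a five-child example with one T3 value missing, a standard routine returned no statistic. It gave a value (5.14, p = 0.076) only after that child's whole row was removed.

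**Step 2: counts.** Complete triples = 30 × (1 − loss at T2) × (1 − loss at T3). T1-T2 pairs = 30 × (1 − loss at T2).

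| Loss at T2 | Loss at T3 | Complete triples | T1-T2 pairs | Pairs discarded |
|---|---|---|---|---|
| 0 | 20% | 30 × 0.8 = 24 | 30 | 6 |
| 0 | 30% | 30 × 0.7 = 21 | 30 | 9 |
| 10% | 20% | 30 × 0.9 × 0.8 = 21.6 | 27.0 | 5.4 |
| 10% | 30% | 30 × 0.9 × 0.7 = 18.9 | 27.0 | 8.1 |

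The loss rates are assumptions; the article gives none.

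**Step 3: power under random loss.** Simulation, 30 children, two-sided 5%. Assumed, not from the article: baseline mean 3.5, SD 1.2 at each visit, correlation 0.6, gain 0.6 (0.5 SD) at T2 and T3, scores rounded to the RF scale.

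| Setting | Friedman power |
|---|---|
| No missing visits | about 78% |
| 10% missing at T2, no T3 loss | about 73% (71% to 73% over repeated runs) |
| 10% at T2, 20% at T3 | about 62% |
| 10% at T2, 30% at T3 | 55% to 57% |

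The fair starting point for the effect of T3 loss is about 73%, because a child missing T2 has no T1-T2 pair to lose. T3 loss therefore costs about 73 − 62 = 11 points at 20%, and 16 to 18 points at 30%. A Wilcoxon signed-rank test on all available T1-T2 pairs stays at about 73%, since it does not depend on T3.

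**Step 4: selective loss.** Same settings, but children with no T1-T2 gain miss T3 at 1.6 times the average rate and the others at 0.4 times (ratio 1.6 / 0.4 = 4). The mean T1-T2 gain among completers is then about 0.74 at 20% loss and 0.84 at 30%, against 0.60 in all pairs. The excess is 0.14 and 0.24 points.

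**Step 5: a second data model.** Assumed: between-child SD 1.0, SD of true individual change 0.8, error SD 0.7, all loss after T2. With a true mean change of zero, a significant Friedman result with RF rising occurs in 2% to 4% of runs with all 30 children. It occurs in 11% to 31% if the poorer responders make up a 20% loss. Under random loss there is no bias. The direction agrees with step 4; the size depends on the model.

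**The case against.** The article calls the study explorative and disclaims generalisation, and missing-data rules are commonly left to an analysis plan that is not shown. That is fair as far as silence goes. But the deletion here follows from the named test. A later plan could add a T1-T2 analysis, yet the primary test as published would still drop these children unless it is replaced or values are imputed.

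Four stronger readings are tempting and are not supported:

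- **That the children lost are the poorer responders.** No section says who leaves. The remark on impermanent placements concerns attachment in general, not attrition in this study, and a change of placement need not track RF gain. If better responders left, the bias would reverse. Section 2.2 requires at least six months in foster care, and the Discussion lets children rejoin the group only after T3. The first favours stable placements and the second gives a reason to attend, which may reduce loss. The second could also make attendance selective, but that is inference.
- **That T3 loss takes power from 78% to 62%.** The first 5 points or so come from the assumed missing T2 visits.
- **That the trial will report an inflated pre-post gain.** Friedman is an omnibus rank test and yields no mean change. Section 2.6 plans descriptive statistics and does not restrict them to completers. What the article fixes is the sample of the primary test.
- **That children who stop or move are not followed.** Nothing says so.

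It is also fair that the rank test was chosen because RF is ordinal. A linear model as the main replacement would set that reason aside.

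**Conclusion.** The point holds in a limited form. As written, the primary analysis of child RF uses only children with all three interviews and discards observed T1-T2 changes of children missing at T3. That follows from the test and needs no assumption.

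The size is conditional. Under the assumed SD, correlation, effect and loss rates, 5.4 to 8.1 of 27.0 pairs go unused and Friedman power falls by about 11 to 18 points. A bias arises only if attendance at T3 is related to change; its direction is unknown, and the 0.74 and 0.84 figures illustrate one assumed mechanism. This merits a change before analysis but does not invalidate the study.

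**What to change.** In section 2.6, analyse child RF with a method that uses all available visits. The preferred choice is an ordinal mixed model with visit as factor and a child random effect, which keeps to the authors' reason for a rank test; a linear version can serve as sensitivity analysis. At minimum, add a prespecified Wilcoxon signed-rank test of T1 against T2 on all available pairs, and state its status beside the primary test. Report T1-T2 and T1-T3 separately, each with its n. Keep Friedman on completers as a supporting analysis.

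The cost is changed wording. SPSS 27, the software named in the article, can fit such models, and no children or visits are added. There are limits:

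- The ordinal model may be unstable with 30 children and about ten RF levels.
- The linear model treats RF levels as scores.
- Either model corrects the T3 result only if loss depends on observed scores.
- Using all T1-T2 pairs removes bias from later T3 loss but not from loss before T2.
- Neither mixed model was simulated here, so the recoverable power is shown only for the signed-rank test.
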